**Interim analyses {21b}**

The interim analyses will be done after 15 patients enter in both intervention groups. After three unexpected serious adverse events in the intervention group leading to increase in the length of stay in the hospital, or one death event in both intervention groups, the main coordinator will check all procedures and report the results to the University committee, as well as he will make the final decision to terminate the trial for safety concerns.

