**Sample size {14}**

Based on the proposed effect size from previous studies (10) and assuming a two-sided 5% significance level and a power of 80%, 35 patients will be our sample size in each group. The target sample size will be 105 critically ill COVID-19 patients, which will be allocated randomly in three trial arms with 35 patients in each group. Patients will be allocated into study groups using a simple randomization method.

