**Adverse event reporting and harms {22}**

In case of any side effect or adverse event in each subject, a report will be written in detail and the main investigator will send the report to the steering committee of the study and the ethics committee of the University. For discharging patients, any complications associated with the study will be followed for one month. The main investigator will evaluate any life-threatening event leading to death. However, this randomized clinical trial will setup on severe COVID-19 patients who have a high mortality rate. For this reason, the cause of death of a patient will first be investigated and the causes will be reported. If it relates to the trail, the research will stop immediately.

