**Discussion**

There are many questions about the treatment and effectiveness of used drugs in this COVID-19. Regarding the treatment of the disease, the issue of ARDS and Cytokine storm should be considered. ARDS acts as an important cause of death in critically ill patients of COVID-19. Cytokine storm and inflammatory mediators are two main suspects for this condition (3,4). All of these can lead to lung damage. Therefore, before extensive damage to lung tissue, clinical therapies should be considered on the control of the responses of the immune system and suppressing the inflammation, in critically ill patients. Theoretically, corticosteroids could help to reduce the incidence of ARDS and consequently the mortality rate (4). But their therapeutic effects and advantages and disadvantages are still in the mist.

Results of previous experiences in influenza and SARS and little new experiences in the management of COVID-19 are inconsistent, especially about the prescription time and number of corticosteroids in different phases of ARDS in the diseases. Use of corticosteroids in all cases of influenza or both SARSs may lead to secondary superinfections and increase mortality rate (12) and patients should be monitored very carefully and the medication should be given at the appropriate time. Besides, high-doses corticosteroids therapy may induce a worse outcome (13). However, the aggregation of the results of different studies indicates an improvement in disease outcomes using early doses of corticosteroids in critically ill patients. One systematic review evaluated the results of ARDS patient data from randomized trials and showed prolonged corticosteroid treatment improved clinical outcomes (14,15). Another randomized controlled trial study showed that corticosteroid therapy could down-regulate inflammation mediators in ARDS and reduce the duration of mechanical ventilation and staying in ICU (14). Surviving Sepsis Campaign has also recommended the use of corticosteroids if the patient is in the cytokine storm condition and if the patient has not yet developed ARDS (16). Some experiences from SARS showed that convalescent plasma or IV-IG can improve the survival rate of patients when they were treated with pulsed methylprednisolone. In this regard, we can use IV-IG to reduce the side effects of corticosteroids (15).

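### The non-fatal limb of the safety trigger counts an unexpected serious adverse event only if it lengthens the hospital stay, with no reference stay given, so serious events that do not prolong a stay go uncounted

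*Protocol*

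**What the plan says.** The trigger stands in the protocol under Interim analyses {21b}. Its first limb is "After three unexpected serious adverse events in the intervention group leading to increase in the length of stay in the hospital". The same sentence goes on, "or one death event in both intervention groups", and when either limb is met "the main coordinator will check all procedures and report the results to the University committee"; that person also takes the final decision on ending the trial for safety. The preceding sentence sets the interim look: "The interim analyses will be done after 15 patients enter in both intervention groups".

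Three other sections bear on the point:

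- **Adverse event reporting and harms {22}** has any adverse event written up and sent to the steering and ethics committees, with no length-of-stay condition. It adds: "For discharging patients, any complications associated with the study will be followed for one month". It also stops the trial for a death found to be related to it.
- **Plans to promote participant retention and complete follow-up {18b}** continues outcome collection to one month after discharge.
- **Composition of the data monitoring committee {21a}** sets up a team that reviews safety in three steps.

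On size, Sample size {14} states "35 patients will be our sample size in each group", which gives 70 patients on the two intervention arms.

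**The concern.** Seriousness and prolongation of stay are different things. Under the non-fatal limb, an unexpected serious event must also lengthen the hospital stay before it counts towards three. That has two consequences.

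First, an increase needs a comparator, and none is stated. Length of stay is a secondary outcome that treatment may itself change. The background section cites a study in which corticosteroid-treated patients had shorter stays. A patient with a serious event might still go home no later than other patients do, and two assessors could score that event differently.

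Second, a serious event after discharge that does not prolong a stay falls outside the count. The protocol does not say whether a readmission counts as an increase.

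This limb is the only numerical trigger the protocol sets for non-fatal harm. If many serious events fail the condition, it fires later or not at all, although the events are already known to the trial.

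**Working it through.** The protocol states no serious-event rate and no target chance of triggering, so there is no figure of its own to reproduce. Its "assuming a two-sided 5% significance level and a power of 80"% concerns efficacy and plays no part in the trigger. The calculation below shows only how strongly the length-of-stay condition can act.

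**Inputs from the protocol**

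- Threshold: three counted events (Interim analyses {21b}).
- Patients at the interim look: 15 in each intervention group, n = 2 × 15 = 30. The sentence can also be read as 15 in total.
- Patients over the whole trial: n = 2 × 35 = 70 (Sample size {14}).

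**Assumptions**

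- Share of patients with an unexpected serious event: r = 20% or 10%.
- Share of those events that meet the length-of-stay condition: f = 1 (every event counts) or f = 1/2.
- The two intervention groups are pooled, patients are independent, and each has at most one event.

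**Formula.** With p = r × f,

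P(at least 3) = 1 − [(1−p)^n + n·p·(1−p)^(n−1) + (n(n−1)/2)·p²·(1−p)^(n−2)].

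**Numbers for n = 30**

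- p = 0.20: 1 − (0.0012 + 0.0093 + 0.0337) = 0.956
- p = 0.10: 1 − (0.0424 + 0.1413 + 0.2277) = 0.589
- p = 0.05: 1 − (0.2146 + 0.3389 + 0.2586) = 0.188

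**Numbers for n = 70**

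- p = 0.20: about 1.000
- p = 0.10: 1 − (0.0006 + 0.0049 + 0.0187) = 0.976
- p = 0.05: 1 − (0.0276 + 0.1016 + 0.1845) = 0.686

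| Assumed rate r | n | All events count (f = 1) | Half qualify (f = 1/2) |
|---|---|---|---|
| 20% | 30 | 96% | 59% |
| 20% | 70 | about 100% | 98% |
| 10% | 30 | 59% | 19% |
| 10% | 70 | 98% | 69% |

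If the interim look is at 15 patients in total, the values at r = 20% are 60% (f = 1) and 18% (f = 1/2).

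**The death limb.** On a pooled reading, P(at least one death in 30) = 1 − (1−m)^30. At an assumed mortality m of 10% this is 1 − 0.9^30 = 0.958; at 20% it is 0.999; at 2% it is 0.455. If the wording instead requires a death in each group of 15, the chance is [1 − (1−m)^15]²: 0.631 at 10% and 0.068 at 2%. The protocol calls mortality high but gives no figure.

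**The case against.** The strongest reply is that the trigger as a whole is not blind. A reader might infer that it can stay silent while patients die, because a fatal event does not lengthen a stay. The text does not support that. The same sentence has a one-death limb, and the adverse-event section stops the trial for a related death. With 30 intervention patients, an assumed 20% rate of non-fatal serious events, half of them qualifying, and pooled deaths, both limbs are silent with probability 0.014 at 10% mortality and 0.0003 at 20%. Silence becomes likely only at low mortality (0.217 at 2%) or if a death is needed in each group.

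Three further inferences also fail:

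- **Events in patients still in hospital cannot be scored.** Nothing requires waiting for discharge, and a clinician can judge prolongation at the bedside. The fair criticism is that the judgement has no stated basis.
- **The word *unexpected* excludes infection.** The Discussion says corticosteroids "may lead to secondary superinfections and increase mortality rate", but that is background literature on their use in influenza and SARS. The protocol contains no list of expected events, so this passage does not settle what counts. Limiting a trigger to unexpected events in very ill patients is a defensible choice.
- **The loss seen at 30 patients is the loss for the trial.** The trigger is not tied to the interim sample. Over 70 patients the fall at a 20% rate is only from about 100% to 98%.

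It is also true that every adverse event is reported to two committees and that the monitoring team looks three times. These safeguards limit the consequence. They do not replace the limb, because neither section sets a count for non-fatal events.

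**Conclusion.** The point holds for the non-fatal limb only. That limb rests on an increase in stay with no comparator, and it leaves out unexpected serious non-fatal events that do not prolong a stay, including such events during the one-month follow-up. Under the assumed rates, if half of the events fail the condition, the chance of reaching three falls by 37 to 40 percentage points at 30 patients (96% to 59%, or 59% to 19%). Over the full 70 the fall ranges from about 2 points at a 20% rate to 29 points at a 10% rate (98% to 69%). The cost is therefore mostly delay when events are common, and a real chance of never triggering when they are less common.

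The event rate, the qualifying share and the pooling of the two arms are all assumptions. That the condition exists, has no reference stay and excludes non-prolonging events rests on the protocol's text alone.

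**What to change.** Under Interim analyses {21b}, remove the length-of-stay condition from the counting rule. Unexpected serious adverse events in the intervention groups would then count at onset, from randomisation to the end of the one-month follow-up. Keep the restriction to unexpected events.

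Reconcile this section with the follow-up {18b}, monitoring {21a} and adverse-event {22} sections, so that all four agree on which events count and over what period. In the same edit, settle the wording: the non-fatal limb refers to one intervention group and the death limb to both.

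The number of events that prompts a review, and anything that follows clinically, stay with the sponsor and the monitoring team.

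The cost is small. The events are already reported, so no new data are needed. More of them will count, and reviews will be prompted somewhat more often.

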**Methods for additional analyses (e.g. subgroup analyses) {20b}**

One of the researchers in our team will evaluate all data extracted from HIS and check the missing data. If possible, the subgroup analyses will be done based on the results.

**Methods in analysis to handle protocol non-adherence and any statistical methods to handle missing data {20c}**

Any missing data in the HIS information will be completed by a telephone interview, if possible. Protocol modifications and study subjects' replacement will not be expected. All primary and secondary outcomes, as well as adverse events, will be done as the intention-to-treat principle.

**Plans to give access to the full protocol, participant level-data and statistical code {31c}**

The full text of the protocol will be available after a formal and reasonable request to the corresponding author by email. Statistical data will be available 10 months after publication of the results in a scientific journal. The request for access to the de-identified patients' information will be reviewed by the team and will be accepted or rejected by reason.

**Oversight and monitoring**

**Composition of the coordinating center and trial steering committee {5d}**

The Coordinating Center (CC) will contain the main investigator who is an internal medicine specialist and an epidemiologist as a methodologist. These persons will report the result to the sponsor and the president of the Golestan University of Medical Sciences to use the result for the establishment of a new COVID-19 treatment algorithm. The trial steering committee will consist of the main investigator, internal specialists, infectious disease specialists, rheumatologists, radiologists, microbiologists, and study statisticians. The steering committee will supervise the trial and make a network for communication between the whole dependent and independent researchers and health workers. They will train everyone involved in the study.

**Composition of the data monitoring committee, its role and reporting structure {21a}**

A data monitoring team will evaluate the results, study safety, and data endpoints independently from the sponsor or any other groups. This team will contain one statistician and a clinician. The team will evaluate the data independently in three steps during the project progress and report only the final results to the sponsor.

**Adverse event reporting and harms {22}**

In case of any side effect or adverse event in each subject, a report will be written in detail and the main investigator will send the report to the steering committee of the study and the ethics committee of the University. For discharging patients, any complications associated with the study will be followed for one month. The main investigator will evaluate any life-threatening event leading to death. However, this randomized clinical trial will setup on severe COVID-19 patients who have a high mortality rate. For this reason, the cause of death of a patient will first be investigated and the causes will be reported. If it relates to the trail, the research will stop immediately.

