**Introduction**

**Background and rationale {6a}**

Coronavirus Disease 2019 (COVID-19) appeared in Wuhan, Hubei, China in December 2019 and the disease spread rapidly around the world since January 2020 and became a pandemic in March 2020. Severe acute respiratory syndrome coronavirus 2 (SARS-CoV-2) (formerly known as 2019-nCoV) is the etiology agent of the disease (1). The COVID-19 infected more than 6700000 individuals all around the world and more than 390000 of them have died, which makes an extraordinary time for our planet. The disease has put a lot of pressure on health care systems, because the number of patients is increasing exponentially, especially in the early days of the spread of infection in each area. Besides, there is no still vaccine or proven effective anti-viral therapy for the disease to help the clinicians to manage it. There is little information about disease management in critically ill patients. The World Health Organization (WHO) and the United States Center for Disease Control and Prevention (CDC) are still working and researching on the best guidance for the management of COVID-19 (2).

Currently, the Ministry of Health and Medical Education (MOHME) of Iran recommends a combination of different antiviral drugs including KALETRA (lopinavir and ritonavir), atazanavir and ritonavir with interferon-beta for the treatment of COVID-19 cases along with supportive therapy. However, this guideline emphasizes that the therapeutic effects of these drugs have not been conclusively proven [Available from: http://dme.behdasht.gov.ir].

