**Intervention description {11a}**

The study subjects will be randomly allocated in three treatment arms and divided into two experimental groups (two arms: intervention 1 and intervention 2) and one control group, which will be matched for age and sex using frequency matching method (Figure 1). Each eligible patient in the control arm will be received the standard treatment for COVID-19 (a combination of antiviral drugs) and the usual standard of care according to the protocol of MOHME of Iran. If the proposed standard treatment is changed, all patients will receive a new suggestion for further treatment. Each patient in the intervention 1 group will receive the standard treatment for COVID-19 and dexamethasone, (as described below), during the first 24 hours of admission. The dexamethasone will be administrated base on the level of SpO2. If the level of SpO2 does not improve after 24 hours, IV-IG and interferon-beta will be prescribed as shown below along with dexamethasone administration. In the intervention 2 group, the administration of dexamethasone will be started at the first 24 hours of admission and will be continued until 48-72 hours and the level of SpO2 will be checked. Then, if the level of SpO2 does not improve after that time, IV-IG and interferon-beta will be prescribed as the same.

Drug dosages and duration of the regimes are stated below for each intervention group. The intervention begins with the administration of dexamethasone:

If the percentage of the SpO2 level is between 85 and 90, the dosage will be 4 mg every 12 h,

If the percentage of the SpO2 level is between 80 and 85, the dosage will be 4 mg every 8 h,

If the percentage of the SpO2 level is between 75 and 80, the dosage will be 8 mg every 12 h,

If the percentage of the SpO2 level is less than 75, the dosage will be 8 mg every 8 h.

The doses of IV-IG will be 400 mg/kg once daily for 5 days and interferon-beta will be 7 doses every other day. As a note, before the IV-IG administration, the level of IgA will be checked.

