**Assignment of interventions: Blinding**

**Who will be blinded {17a}**

The PI is unblinded and is responsible for the study and will handle all team. However, this person will not play a role in examining the data and interpreting the results. An unblinded researcher (a pharmacist) will cover the drug’s bottles with aluminium foil and prepare them interventions and control drugs in a syringe with a code so that patients are blinded. This person will not be in contact with patients. The staff and nurses, caring for the patients, will be unblinded for each study group due to the nature of this study. The staff that take outcome measurements will be blinded. The laboratory technicians will also be blinded as well as the statistical team. These study statisticians will have access to coded data and will analyse the data labelled as group X, group Y, and group Z.

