**Plans to promote participant retention and complete follow-up {18b}**

All related data about the outcomes including the daily level of SpO2, vital status, intubation status, the hospital stay length, and the time of discharge will be obtained during the hospitalization, day 14, and followed up one month after the discharge time. The data will be obtained by HIS, physical visit on a bed or a telephone interview. The main coordinator will provide written feedback and send an acknowledgment to the participants or their families. Besides, all cases who withdraw their study participation will be followed one month and If they need management and health services, they will be taken care of. Moreover, information from people who have dropped out of the study will also be checked if they have received enough doses of the drugs and will not be replaced by other patients.

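### Harms follow-up after discharge depends on an undefined judgement of association with the study, so late non-fatal harms may be captured unequally between arms or under-counted in all of them

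*Protocol*

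**What the plan says.** The Protocol's section on adverse event reporting and harms {22} holds two rules, one after the other. The first is general: "In case of any side effect or adverse event in each subject, a report will be written in detail". It has no causality condition and no end date. The second is the only harms rule specific to the time after discharge: "For discharging patients, any complications associated with the study will be followed for one month". Association is not defined, and neither the person who decides nor that person's blinding is stated.

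The section on retention and follow-up {18b} lists the outcome data to be obtained in hospital, at day 14 and one month after discharge: "the daily level of SpO2, vital status, intubation status, the hospital stay length, and the time of discharge". No adverse-event or infection item is on the list.

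The section on non-adherence and missing data {20c} nevertheless commits to an analysis of harms by arm: "All primary and secondary outcomes, as well as adverse events, will be done as the intention-to-treat principle". The Discussion names the late harm of most interest, saying that corticosteroids "may lead to secondary superinfections and increase mortality rate (12) and patients should be monitored very carefully".

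**The concern.** A comparison of harms between arms needs the same chance of capture in every arm. A condition that rests on judged association may not give that. The intervention description {11a} assigns dexamethasone, and IV-IG if SpO2 does not improve, to the two intervention arms. For the control arm it says: "Each eligible patient in the control arm will be received the standard treatment for COVID-19 (a combination of antiviral drugs"). An infection three weeks after dexamethasone is easy to link to the trial; the same infection in a control patient is harder to link.

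Superinfection can rarely be attributed with confidence in one patient. It shows as a difference in frequency between arms, and that difference is what unequal capture distorts. A statistical analysis plan could not repair this later, because events that were never collected cannot be analysed. The stake is limited to non-fatal harms after discharge, but the Abstract says that the trial will try to show the drugs' disadvantages as well as their effectiveness.

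**Working it through.** **Does another section repair the gap?**

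- {22}, first sentence: would cover all events if read without a time limit, but the next sentence sets a different criterion for discharged patients.
- {18b}: one-month follow-up of participants, without an adverse-event item.
- {13}: patients discharged before day 14 are monitored by phone or home visit, for outcome factors. The outcomes in {12} are SpO2, length of stay, intubation and ventilation, and mortality.
- {11d}: a daily check, worded as a check for drug side effects.
- {16c}: two blinded nurses make the follow-up contacts, but nothing tells them to ask about all events.

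None of these sets up collection of all late adverse events in every arm.

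**Size of a possible bias.** The protocol has no figure to reproduce here: it gives no late-event rate and no capture fraction. The only inputs from the document are 35 patients per arm and the two-sided 5% level (Sample size {14}). Fisher's exact test is named in {20a}. The rest is assumed.

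Let p be the true late-event risk, equal in both arms, and let s_T and s_C be the fractions captured in an active arm and in control.

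- Expected recorded events per arm = 35 × p × s
- Spurious risk difference = p × (s_T − s_C)
- Chance of p ≤ 0.05: the exact Fisher test, summed over Binomial(35, p·s_T) and Binomial(35, p·s_C)

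| True risk | Capture, active v control | Expected events, 35 v 35 | Spurious difference | Fisher p ≤ 0.05 |
|---|---|---|---|---|
| 5% | 100% v 100% | 1.75 v 1.75 | 0 | 0.3% |
| 5% | 80% v 20% | 1.4 v 0.35 | 3 points | 0.2% |
| 5% | 80% v 0% | 1.4 v 0 | 4 points | 0.2% |
| 10% | 100% v 100% | 3.5 v 3.5 | 0 | 1.3% |
| 10% | 80% v 50% | 2.8 v 1.75 | 3 points | 1.2% |
| 10% | 80% v 20% | 2.8 v 0.7 | 6 points | 3.0% |
| 10% | 80% v 0% | 2.8 v 0 | 8 points | 5.7% |
| 20% | 100% v 100% | 7.0 v 7.0 | 0 | 2.5% |
| 20% | 80% v 50% | 5.6 v 3.5 | 6 points | 5.4% |
| 20% | 80% v 20% | 5.6 v 1.4 | 12 points | 21.0% |
| 20% | 80% v 0% | 5.6 v 0 | 16 points | 49.7% |

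One row can be checked directly. With no recorded control events, 5 of 35 gives a Fisher p of 0.054 and 6 of 35 gives 0.025, so at least 6 are needed. At a true 20% and 80% capture, the chance that Binomial(35, 0.16) reaches 6 is 0.497.

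**If the condition is applied equally.** With 30% capture in both arms the spurious difference is zero, but a true 20% v 10% would be recorded as 0.3 × 20 = 6% v 0.3 × 10 = 3%. A real 10-point excess then appears as 3 points.

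**The case against.** Four stronger readings are tempting, and the text does not support them.

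**That only associated complications are collected after discharge.** That word is not in the protocol. The first sentence of {22} covers every subject and does not end at discharge. The two sentences are unreconciled; the second does not clearly exclude other events. The phrase could even be read loosely as covering any complication in a participant. This stands, but sites could follow either sentence, so the text still needs repair.

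**That controls receive no study drug.** The background {6a} describes a national standard that includes "atazanavir and ritonavir with interferon-beta for the treatment of COVID-19 cases along with supportive therapy", and interferon-beta is a study drug. The blinding section {17a} also has an unblinded pharmacist "prepare them interventions and control drugs in a syringe with a code so that patients are blinded". What can be said is that controls are assigned no dexamethasone or IV-IG, which is enough for the superinfection argument.

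**That the comparison is biased, with harm overstated in the active arms.** The follow-up nurses and the staff who measure outcomes are blinded ({16c}, {17a}), and a blinded assessor cannot easily apply an arm-dependent condition. Care staff are unblinded, however, and the protocol does not say who judges association. If events are put down to COVID-19 itself, a real excess would be hidden. Bias is therefore possible but not shown, and its direction is not fixed.

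**That the false-signal risk is as high as 37% to 89%.** Those figures follow at a true risk of 20% if the two intervention arms are pooled (70 v 35) and capture is 80% v 20% or 0%. Section {20a} does not state pooling. Arm against control, the figures are 21% to 50%, and they fall quickly under milder assumptions.

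The gravest harms also lie outside this sentence. Mortality and intubation are secondary outcomes, vital status is followed for one month after discharge, and {22} has causes of death investigated and reported.

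**Conclusion.** The point holds as a possible ascertainment gap for non-fatal harms after discharge. The protocol ties that follow-up to an undefined, unassigned judgement, does not reconcile it with the general reporting rule beside it, and lists no follow-up item that would fill the gap. Capture may differ between arms, in which case the intention-to-treat analysis of adverse events may be biased; or it may be low in all arms, in which case a real excess is diluted.

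The size rests wholly on assumed rates. At 35 v 35 with 80% v 0% to 20% capture, the chance of a spurious excess is 3% to 6% at a true risk of 10% and 21% to 50% at 20%. With 80% v 50% capture it is about 1% and 5%, close to the 1.3% and 2.5% found with full equal capture. At a true 5% it is negligible. The text should be changed, but the primary outcome, mortality and intubation do not depend on it.

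**What to change.** In {22}, reconcile the two sentences. Replace the condition on association with the study by wording such as: *all adverse events, including any new infection, in all three arms, regardless of suspected relation*. Keep the one-month window.

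Have the blinded research nurses of {16c} collect these events with the same questions in every arm, at the visits or calls already scheduled in {16c} and {18b}. Add adverse events and new infections to the list in {18b}. Record relatedness as a separate field, not as a condition for entry, and state who judges it and whether that person is blinded.

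With equal capture the spurious difference p × (s_T − s_C) is zero at any true risk. The cost is a few lines of protocol text and a few questions at existing contacts. The small downside is more reported events, most of them from the underlying disease.
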